### Randomisation and allocation concealment

To avoid contamination, we will use cluster randomisation using schools as the randomisation unit. Schools will be allocated to either arm of the study using block randomisation with a block size of four. This will be performed by an independent researcher. Group allocation will only be revealed to participants following the collection of baseline data.

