### Participant recruitment and baseline assessment

The study will take place in approximately ten schools across England. All schools will be comprehensive secondary schools and have a standard Sex and Relationships (SRE) policy and SRE curriculum in place.

Researchers will make contact with SRE co-ordinators at the schools who will describe the study and invite participation. SRE co-ordinators who wish to participate will be required to obtain permission from the school head teacher. They will be asked to identify classes receiving SRE in their school where pupils are aged 13–16 years old. SRE teachers must confirm that the chlamydia lesson has not previously been delivered to these pupils and that they have not received any teaching on STIs. Full details on the requirements of participating schools will be provided. Schools will be offered a £100 Amazon voucher in recognition of the time and resource commitment required. They will also be offered an individual school report based on anonymised and aggregated pupil data from this study which may be helpful in informing their SRE policy and curriculum.

Participating SRE teachers will schedule one lesson (45 minutes) per class to provide study information, obtain consent and collect baseline measures. Pupils will be told that the study aims to evaluate teaching on STIs in their school, but not informed that there are two intervention arms. Pupils will also be told about the number and nature of assessments that will be made, and how their data will be protected and treated. They will be provided with a written participant information sheet and asked to sign a consent form.

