Pupils will not be obliged to take part. Quizzes will be administered at the same time as questionnaires at all data collection time points to occupy pupils who do not wish to participate. Pupils will not be required to provide their name (participant responses at each time point will be linked through the demographic information supplied). Pupils will be seated in a manner that prevents classmates from overseeing their responses i.e. in exam conditions. All materials (questionnaires and quizzes) will be placed in a sealed envelope by the individual participants and posted into sealed boxes on completion. Teaching staff will not have access to these. Although parental consent will not be required, as parents of participating pupils will have already consented for their children to participate in SRE and related evaluation activities, a letter outlining the study and their child’s involvement will be sent to all parents through each school as a matter of courtesy. Parents will be given the opportunity to ‘opt-out’ their child at this point.

Baseline measures will be: Demographic information (age, date of birth, gender, and ethnicity), perceived likelihood, perceived severity, response efficacy, self-efficacy, past behaviour, and intention to use condoms during vaginal sex with casual sexual partners for whom STI status is unknown. Provisional measures to be taken at baseline, post-intervention and follow-up are provided in Additional file 1.

After the collection of baseline data, schools will be randomised to receive either the school’s usual teaching on STIs and the chlamydia lesson (intervention arm) or the school’s usual teaching on STIs alone (control arm). This enables the study to evaluate the effectiveness of the chlamydia lesson over and above usual practice. As described above, pupils will be blinded to intervention condition. It is not possible to blind teachers to intervention condition but they will be made aware of the importance of delivering teaching that is consistent with their usual practice. Researchers liaising with schools will offer the same guidance and level of support regardless of intervention condition.

As with all trials of this type, there is the potential for drop-out of whole schools during the study. We have no way of estimating the level of this. Drop-out due to unforeseen circumstances will be planned for and a reserve list of schools will be created to expedite the process of additional recruitment if required.

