### Sample size calculation

The calculation is based on the primary research question. Power analysis using GPower 3.1.2 has indicated that 484 participants will provide 95% power to detect a small to medium effect of 0.3 [21] where α = 0.05. The effect size of 0.3 is based on a recent meta-analysis examining the effectiveness of interventions in changing risk appraisals, intentions and behaviour [22]. Due to the tendency for individuals within a cluster to be more similar to each other than those in other clusters, it is necessary to make adjustments to avoid an overestimation of power [23]. In order to obtain this adjusted sample size, the sample size determined by usual procedures is inflated by multiplication with a factor. This factor is known as the “design effect” and is calculated as:

$$1+\left(n–1\right)\mathrm{ICC}$$

where *n* is the average cluster size, and ICC is the intraclass correlation coefficient. The ICC for intention to use condoms between schools is not known but an estimate of 0.01 is reasonably conservative [23]. With ten schools and an average cluster size of 60 (×2 classes of 30 pupils), the design effect is:

$$1+\left(60–1\right)0.01=1.59$$

Accordingly the adjusted sample size is 484 × 1.59 = 770. We will over-recruit to allow for drop-out between the start of the study and the three month follow-up.

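### About ten schools are allocated by unstratified blocks of four, and the baseline data already held before randomisation are not used to balance the arms

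*Protocol article*

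**What the plan says.** Under Randomisation and allocation concealment the protocol article states that "we will use cluster randomisation using schools as the randomisation unit", and then: "Schools will be allocated to either arm of the study using block randomisation with a block size of four". It adds: "This will be performed by an independent researcher". No stratification, matching or other balancing constraint is described.

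On the number of schools, Participant recruitment and baseline assessment says: "The study will take place in approximately ten schools across England". The Sample size calculation works "With ten schools and an average cluster size of 60".

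On timing, Participant recruitment and baseline assessment says: "After the collection of baseline data, schools will be randomised". The baseline measures listed there are demographics, the risk and coping appraisals, past behaviour and condom-use intention. Whether schools are drawn together or one after another is not stated. The same section says that "a reserve list of schools will be created to expedite the process of additional recruitment if required".

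The ANCOVA under Statistical analysis adjusts for gender, ethnicity, age, behaviour at time one, and the risk and coping appraisals. Baseline intention, the baseline value of the primary outcome, is not in that list.

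**The concern.** With about five schools per arm, randomisation alone gives only loose balance on anything that varies between schools, such as the year group entered (classes may be aged 13 to 16) or the level of sexual experience. This trial will hold the baseline of its primary outcome for every school before allocation, which makes balance by design possible at little cost. The stated scheme does not use that opportunity, and the listed covariates leave baseline intention unadjusted as well.

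Two features of the block size matter less. Ten is not a multiple of four, so the last block is cut short and the arms can end up unequal. A fixed, published block size can also make some allocations predictable, but only under conditions that the protocol does not establish.

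**Working it through.** **The plan's own figures.** The design effect is 1 + (60 − 1) × 0.01 = 1.59, and 484 × 1.59 = 769.6, so 770. Both reproduce. The protocol gives no figure for arm split, predictability or balance.

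**Split between arms.** Inputs: blocks of four with two schools per arm (assumed; no other ratio is given) and ten schools. Two full blocks give 4:4, and the third block supplies two places. The probability that both fall in the same arm is 2 × (2/4 × 1/3) = 1/3. So the split is 6:4 with probability 1/3 and 5:5 with probability 2/3. At 8 or 12 schools the split is exact, at 9, 11 or 13 the arms differ by one school, and at 14 the split is 8:6 with probability 1/3.

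**Cost of 6:4.** Relative efficiency is 4 × 0.6 × 0.4 = 0.96. With 60 pupils per school, ICC 0.01, effect 0.3 and a two-sided normal approximation:
- 5:5: SE = √[(1.59/60)(1/5 + 1/5)] = 0.1030; 0.3/0.1030 − 1.96 = 0.95; power 83.0%.
- 6:4: SE = √[(1.59/60)(1/6 + 1/4)] = 0.1051; 0.3/0.1051 − 1.96 = 0.90; power 81.5%.

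**Predictability, if allocation is sequential and earlier allocations are known.** In each full block the fourth place is always determined, and the third is determined when the first two match (probability 1/3). That is 4/3 places per block, so 8/3 = 2.67 of ten, or 26.7%. If all schools are drawn together, no usable prediction remains.

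**Balance on a school-level covariate under the stated scheme.** For independent school values with unit SD, the arm difference has SD √(1/5 + 1/5) = 0.632 at 5:5 and √(1/6 + 1/4) = 0.645 at 6:4. Multiplying by √(2/π) = 0.798 gives mean absolute differences of 0.505 and 0.515. Weighted 2/3 and 1/3, the mean is 0.51 between-school SD. The difference exceeds 1 SD in about 12% of allocations.

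**The same figure for intention.** At ICC 0.01 the between-school SD is √0.01 = 0.10 of the total SD, so 0.51 × 0.10 ≈ 0.05 total SD, against a target effect of 0.3. At an assumed ICC of 0.05 it would be 0.51 × √0.05 ≈ 0.11 total SD. Age may cluster more strongly by school, but the protocol gives no figure for it.

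**Balance under constrained allocation.** There are 252 ways to allocate ten schools 5:5. Drawing at random from the best-balanced quarter (63 allocations), simulation with independent standard-normal school values gives a mean absolute difference of 0.11 between-school SD when one covariate is balanced. When three are balanced jointly it gives about 0.26 for each. The second figure applies to the fix below: 0.26/0.51 is roughly one half.

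**The case against.** The case against acting is substantial. Blocked randomisation of schools with covariate adjustment is a valid design, and imbalance under it is chance variation, not bias. The ANCOVA already adjusts for age, gender, ethnicity, past behaviour and the appraisals. At the protocol's own ICC the school-level imbalance in intention is small. The 6:4 split is specific to ten schools, or fourteen. The article says approximately ten, and 770 pupils at 60 per school is 770/60 = 12.8 schools. At 12 or 13 schools the arms are equal or differ by one. All of this stands, and it limits the point to an optional improvement.

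A reader might infer that about a quarter of allocations can be deduced in advance. The documents do not support that as a flat statement. It needs school-by-school allocation and knowledge of the earlier results, and the article is silent on whether allocation is batched. A reader might also infer that reserve schools would be approached once their arm was foreseeable. The article says only that a reserve list will exist. It does not say who draws on it, or that such schools enter partway through a block. In addition, consent and baseline measurement come before allocation, pupils are not told that there are two arms, and an independent researcher allocates. Even under sequential allocation, foreknowledge could affect only which school enters next, not pupil recruitment or baseline answers.

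What remains is that data suited to balancing the arms will be held before allocation and are not used, while baseline intention is also missing from the listed covariates. Adjustment for the other variables does not fill that gap.

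**Conclusion.** The point holds as a low-severity design improvement. The allocation scheme is valid but makes no use of baseline information collected before randomisation, in a trial with few clusters.

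The expected imbalance on a school-level covariate is about 0.51 between-school SD. For intention this is about 0.05 total SD at ICC 0.01 and about 0.11 at an assumed 0.05. Balancing three covariates would roughly halve it. A gain of four-fifths, from 0.51 to 0.11, applies to one covariate only and should not be expected here. The 6:4 split costs about 4% in efficiency, or 1 to 2 points of power, at exactly ten schools. The predictability figure of 27% is conditional and is not a finding about how this trial will allocate.

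These sizes assume two schools per arm in each block, ten schools of equal size, and independent, normally distributed school values.

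**What to change.** Have the independent researcher randomise all schools in one batch after the last baseline session, in equal numbers per arm. The allocation is drawn at random from those best balanced on school mean baseline intention, mean age and proportion of girls; the best quarter leaves 63 of the 252 possible 5:5 allocations. If timetables prevent a single batch, use two batches, each with an even number of schools, and balance within each. State in the protocol that allocation is batched, which also removes any question of predictability.

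Adjust for the same variables in the analysis. Age and gender are already listed, so the addition is baseline intention.

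The cost is a short script for a person already in place and some waiting for the earliest schools until the batch is complete, which lengthens their interval between baseline and lesson in both arms alike. Sample size, intervention and measures do not change.

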### Sample size calculation

The calculation is based on the primary research question. Power analysis using GPower 3.1.2 has indicated that 484 participants will provide 95% power to detect a small to medium effect of 0.3 [21] where α = 0.05. The effect size of 0.3 is based on a recent meta-analysis examining the effectiveness of interventions in changing risk appraisals, intentions and behaviour [22]. Due to the tendency for individuals within a cluster to be more similar to each other than those in other clusters, it is necessary to make adjustments to avoid an overestimation of power [23]. In order to obtain this adjusted sample size, the sample size determined by usual procedures is inflated by multiplication with a factor. This factor is known as the “design effect” and is calculated as:

$$1+\left(n–1\right)\mathrm{ICC}$$

where *n* is the average cluster size, and ICC is the intraclass correlation coefficient. The ICC for intention to use condoms between schools is not known but an estimate of 0.01 is reasonably conservative [23]. With ten schools and an average cluster size of 60 (×2 classes of 30 pupils), the design effect is:

$$1+\left(60–1\right)0.01=1.59$$

Accordingly the adjusted sample size is 484 × 1.59 = 770. We will over-recruit to allow for drop-out between the start of the study and the three month follow-up.

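### The stated 95% power makes no allowance for testing the arm difference on about ten randomised schools; on 8 degrees of freedom it is about 91% one-sided or 82% two-sided

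*Protocol article*

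**What the plan says.** The sample size section of the protocol article starts from a calculation for independent pupils: "Power analysis using GPower 3.1.2 has indicated that 484 participants will provide 95% power to detect a small to medium effect of 0.3", "where α = 0.05". It names neither the test nor the number of sides. It recognises clustering, saying "it is necessary to make adjustments to avoid an overestimation of power", and deals with it through a design effect alone: "With ten schools and an average cluster size of 60 (×2 classes of 30 pupils), the design effect is" 1.59, giving an adjusted total of 770. The intraclass correlation is an assumption: "The ICC for intention to use condoms between schools is not known but an estimate of 0.01 is reasonably conservative".

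Under randomisation and allocation concealment the article says "we will use cluster randomisation using schools as the randomisation unit". Under participant recruitment it says "The study will take place in approximately ten schools across England". No allowance for the small number of schools appears in the calculation.

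**The concern.** A design effect enlarges the sample so that the arm difference has the variance it would have had with 484 independent pupils. It leaves the critical value where a test on several hundred degrees of freedom puts it. When schools are randomised, the error for the arm comparison includes variation between schools, which has to be estimated from the schools themselves. Ten schools in two arms give 10 − 2 = 8 degrees of freedom, so the critical value is appreciably larger and power lower.

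This matters for interpretation. At 95% power, a null result on condom use intention would be read as strong evidence against an effect of 0.3. With the lower power that evidence is weaker, although the section says it adjusts so as not to overstate power.

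**Working it through.** **Inputs.** From the sample size section: standardised effect d = 0.3, α = 0.05 with sidedness not stated, N = 484, ICC = 0.01, average cluster size 60, ten schools, adjusted total 770. From the randomisation section: the school is the unit. Equal arms and no gain from covariates are my assumptions.

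**Formula.** Power from the noncentral t distribution, with noncentrality d × √(N_eff / 4) and the stated degrees of freedom (df).

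**Step 1: reproduce the plan's figures.** With N = 484 the noncentrality is 0.3 × √121 = 3.30.
- One-sided, 482 df, critical value 1.65: power 95.06%. N = 482 gives 94.99%, so 484 is the smallest even total that reaches 95%.
- Two-sided, 482 df, critical value 1.96: power 90.9%. A two-sided test needs 580 for 95%.
- Design effect 1 + 59 × 0.01 = 1.59, and 484 × 1.59 = 769.6, rounded to 770.

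The arithmetic is therefore right for a one-sided pupil-level t-test.

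**Step 2: change only the degrees of freedom.** Keep 484 effective pupils and noncentrality 3.30.

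| Degrees of freedom | One-sided: critical value, power | Two-sided: critical value, power |
|---|---|---|
| 482 (pupils) | 1.65, 95.1% | 1.96, 90.9% |
| 8 (ten schools) | 1.86, 91.3% | 2.31, 82.3% |
| 11 (13 schools) | 1.80, 92.5% | 2.20, 85.1% |

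The 13-school row is there because 770 / 60 = 12.8. With ten schools the loss due to df is 95.1 − 91.3 = 3.8 points one-sided and 90.9 − 82.3 = 8.6 points two-sided. With 13 schools it is 2.6 and about 5.8 points.

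**Step 3: power for specific ten-school layouts.** These also carry a smaller effective sample, so they illustrate what a restated figure would look like. They do not measure the df effect.
- Ten schools of 60: N_eff = 600 / 1.59 = 377.4. On 8 df, 84.4% one-sided and 72.4% two-sided. On pupil df, 89.7% and 82.9%.
- Ten schools of 77: design effect 1 + 76 × 0.01 = 1.76, N_eff = 770 / 1.76 = 437.5. On 8 df, 88.7% and 78.4%. On pupil df, 93.2% and 88.0%. A simulation of school-mean t-tests for this layout gave 78.4% two-sided.

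**Step 4: what covariates would have to supply.** On 8 df, 95% power needs N_eff of 582 one-sided or 761 two-sided. Starting from 484, that is an R² of 1 − 484/582 = 17% or 1 − 484/761 = 36%. On 11 df the needs are 550 and 701, or 12% and 31%.

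**The case against.** The strongest reply is that the effect is modest. Only a one-sided test reproduces 484, so the loss attributable to degrees of freedom is about 4 points and power stays above 90%; with 13 schools it is under 3 points. That stands, and it limits the weight of the point.

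Second, the planned ANCOVA adjusts for demographics, past behaviour, and risk and coping appraisals, and an R² of 12% to 17% would restore 95% one-sided. That is possible. But the article gives no R² and its calculation takes no credit for one. Over-recruitment and the reserve list of schools are both there to cover drop-out, so neither is spare power.

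Third, a pupil-level ANCOVA would have hundreds of degrees of freedom. It has them only by ignoring the unit that was randomised. The choice of small-sample method may fairly be left to an analysis plan, but the 95% is printed in the protocol and can be checked there.

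A reader might infer more than the article supports, in three ways.
- Setting 78.4% or 88.7% against 95% suggests a shortfall of 6 to 17 points. That range adds in the unstated sidedness and the larger cluster size, which are separate issues.
- Neither figure can simply replace the 95%: both assume 77 pupils per school, where the article states 60.
- The probability beyond ±1.96 on 8 degrees of freedom is about 8.6%, which suggests an inflated false-positive rate. The article nowhere proposes normal critical values with a between-school error, so that figure describes an analysis that is not planned.

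**Conclusion.** The point holds, with a limited size. The arithmetic reproduces, but the method omits the small number of schools, so on the plan's own inputs the 95% is not delivered. With 484 effective pupils and ten schools, power is about 91% one-sided or 82% two-sided; with 13 schools it is about 93% or 85%. This rests on an effect of 0.3, equal arms, no covariate gain, and a school-level test or its mixed-model equivalent. Granting 484 effective pupils also takes 770 pupils at the plan's design effect of 1.59 as given. The difference between 770 pupils and the 600 implied by ten schools of 60, and the undeclared sidedness, should be resolved on their own account and not counted here. The stated power should be corrected, but nothing in this point calls for a different design.

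**What to change.** In the sample size section, replace the 95% with the power of a two-arm comparison on the number of schools minus 2 degrees of freedom. First confirm the number of schools, the cluster size and whether the test is one- or two-sided, because the figure depends on all three. At ICC 0.01 and effect 0.3, ten schools of 60 would read about 84% one-sided or 72% two-sided, and ten schools of 77 about 89% or 78%. State that no covariate gain is counted.

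In the analysis section, or in the analysis plan if one exists, add one sentence: the primary comparison uses school-level degrees of freedom or an equivalent small-sample correction in a mixed model.

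The cost is a rewritten paragraph and one added sentence, a less favourable stated power and a slightly wider confidence interval. This correction needs no extra pupils or schools.

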## Methods/design

A two-arm cluster randomised controlled trial (RCT) using a waiting-list control will be used to test the efficacy of an intervention to increase young adults’ intentions to use condoms and actual use of condoms with casual sexual partners compared to a control group (see Figure 1). Secondary school pupils will be invited to participate. The intervention is a single lesson on chlamydia which aims to increase young adults’ chlamydia risk and coping appraisals. We hypothesise that there will be an increase in condom use intentions following delivery of the chlamydia lesson. At the two month follow-up, we hypothesise that there will be a higher rate of condom use during vaginal sex with casual sexual partners amongst sexually experienced participants in the intervention group compared with the control group. At two months, we will also measure condom use intentions to see whether any increases have been maintained over time. We hypothesise any effects of the intervention on condom use intentions or behaviour will be mediated by risk appraisals and/or coping appraisals.

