Lessons in the control and experimental groups will be delivered by their usual timetabled SRE teacher. Those delivering the chlamydia lesson will be given minimal instruction with regards to delivery as all necessary information is contained within the lesson plan. Fidelity to the lesson plan will be assessed using a self-report checklist completed post-delivery (see Additional file 2).

On study completion, all schools allocated to the control group will be directed to the e-Bug website to enable them to download and deliver the chlamydia lesson if they wish providing the findings do not indicate that the lesson has any detrimental effects i.e. unfavourable changes in any of the primary or secondary outcome measures.

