#### To examine the effect of the intervention

Analysis of Covariance (ANCOVA) will be performed to examine differences in condom use intentions (at time two and at follow-up), and behaviour. This will control for demographic variables (gender, ethnicity, age), behaviour at time one, and measures of risk appraisal, and coping appraisal.

If the lesson is effective in increasing condom use intentions, mediation analysis [28] will be conducted to identify whether changes in risk appraisals and/or coping appraisals are responsible for this change. This will help to identify the mechanism of change and indicate where future research and/or resources should be focussed.

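### The 484 pupils stated for 95% power are reproduced only by an undeclared one-tailed test; two-sided, they give about 91%

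*Protocol article*

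**What the plan says.** The protocol article, under Sample size calculation, states that "484 participants will provide 95% power to detect a small to medium effect of 0.3" "where α = 0.05", computed in GPower 3.1.2. It then multiplies 484 by a design effect of 1.59 (60 pupils per school, ICC 0.01) to reach 770. The effect metric, the allocation ratio, the test family and the number of tails are not given.

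Three other sections bear on the direction of the test:

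- Methods/design words the hypothesis directionally: "We hypothesise that there will be an increase in condom use intentions following delivery of the chlamydia lesson".
- The analysis section says that "Analysis of Covariance (ANCOVA) will be performed to examine differences in condom use intentions". It does not mention a one-sided test.
- The Intervention section lets control schools have the lesson afterwards "providing the findings do not indicate that the lesson has any detrimental effects", which it explains as "unfavourable changes in any of the primary or secondary outcome measures".

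**The concern.** A reader who sees an alpha of 0.05 with no qualifier will take the test as two-sided. On that reading, 484 is too few for 95% power at an effect of 0.3. Either the calculation used one tail without saying so, or the stated power is wrong for the test that will be run.

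Two things are at stake. First, 484 is the base of the whole calculation, so the 770 inherits the problem. Second, the type I error convention of the primary test is left open. A one-tailed test at 0.05 puts the full 5% on a false finding of benefit, whereas a two-sided test puts 2.5% there. That choice should be on record before data are seen.

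**Working it through.** **Inputs.** Power 0.95, effect 0.3 and alpha 0.05 come from the sample size section. Two readings are assumed because the article does not state them: that 0.3 is a standardised mean difference d, and that allocation is 1:1.

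**Formula.** With n pupils per arm, the t statistic has 2n − 2 degrees of freedom and noncentrality d × √(n/2). Power is the probability that it exceeds the critical value: the 0.95 quantile for one tail, or the 0.975 quantile in either direction for two.

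**Step 1: reproduce 484.** At n = 242 the noncentrality is 0.3 × √121 = 3.30.

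| Test | n per arm | Total | Power |
|---|---|---|---|
| One-tailed | 241 | 482 | 0.9499 |
| One-tailed | 242 | 484 | 0.9506 |
| Two-sided | 242 | 484 | 0.9088 |
| Two-sided | 289 | 578 | 0.9495 |
| Two-sided | 290 | 580 | 0.9502 |

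The smallest one-tailed total that reaches 95% is exactly 484. The smallest two-sided total is 580.

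**Step 2: try other readings.**

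- An ANCOVA F test with f = 0.15 (equivalent to d = 0.3 in two equal arms) needs 580, whether 0 or 10 covariates are counted.
- Reading 0.3 as f gives 147.
- Regression F tests with 1 to 7 numerator degrees of freedom, at several effect sizes, gave nothing within 20 of 484.

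**Step 3: size of the gap.** Two-sided, the type II error at 484 is 1 − 0.9088 = 9.1%, against the 5% stated. For comparison, 90% two-sided power needs 470, so 484 would support a claim of 90%.

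**Step 4: carry the figure through the clustering.** The design effect is 1 + (m − 1) × 0.01, where m is the number of pupils per school.

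- With m = 60 the design effect is 1.59, and 770 / 1.59 = 484. So 770 pupils carry the 91%, but 770 / 60 = 12.8, which means about 13 schools.
- With ten schools, m = 77 and the design effect is 1 + 76 × 0.01 = 1.76. The effective number is 770 / 1.76 = 437.5 and the noncentrality is 0.3 × √(437.5 / 4) = 3.14. Two-sided power is about 88%. Using 10 − 2 = 8 school-level degrees of freedom (critical value 2.306), it is about 78%.
- Keeping 95% two-sided needs 580 × 1.59 = 922.2, so 923 pupils. That again assumes 60 per school (923 / 60 = 15.4, so about 16 schools). Spread over ten schools, 923 pupils have m = 92.3, a design effect of 1.913 and an effective number of about 482.

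**The case against.** The strongest reply is that no sum is wrong. 484 is the correct answer for a one-tailed test, and both the research question and the hypothesis are worded as an increase. The article condenses a fuller document, which may name the tails. This stands in part: a one-tailed test could be defended. But a directional hypothesis does not declare a one-tailed test, and the published sentence makes a numerical claim that fails on the usual reading of alpha.

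A reader might infer that the ANCOVA is two-sided by construction, so that the protocol contradicts itself. The documents do not support that. With two arms the treatment effect has one degree of freedom, and the same model gives a t statistic that can be read in one tail. Nor does the condition about detrimental effects commit the trial to a two-sided primary test. It governs release of the lesson after the study and names no significance test. It does show that harm matters to a decision, which sits poorly with an undeclared one-tailed test.

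A one-tailed test at 0.05 would also not breach the declared alpha. The 2.5% is a convention, not a figure in the protocol.

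Finally, the planned adjustment could recover the loss. A multiple correlation of about 0.41 between covariates and outcome gives 580 × (1 − 0.41²) = 482.5, close to 484; a correlation of 0.3 gives about 93% power. This is fair, but the sample size section claims no such gain.

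**Conclusion.** The stated 95% holds only under a one-tailed test that the protocol does not declare. With the conventional two-sided test and no covariate gain, 484 independent pupils give about 91%.

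That the calculation was one-tailed is an inference from the exact match. It rests on d = 0.3 and 1:1 allocation, and on no other reading tried giving 484. The inference is strong, but it is not a documented fact.

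A reader might conclude that the trial is underpowered for this reason alone, or that it must recruit more. Neither follows: about 91% is respectable and the loss is about four percentage points. Nor should 91% be attached to 770 pupils without a condition. It needs about 13 schools of 60, and it makes no allowance for the small number of clusters. This should be fixed, but it is not a fatal flaw.

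**What to change.** Declare the primary test two-sided at alpha = 0.05, and restate the power for 484 independent pupils as about 91% instead of 95%. Name the effect metric and the allocation ratio in the same sentence.

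Attach the 91% to 770 pupils only if the cluster size stays at 60, and say that this means about 13 schools. If about ten schools are kept, recompute the design effect and report the lower two-sided power: for 770 pupils, a design effect of 1.76, an effective number of about 438, and about 88% (about 78% with 8 school-level degrees of freedom).

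If a one-tailed test was truly intended, the protocol must say so, justify it given its own interest in unfavourable effects, and match it in the analysis section.

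The cost is a sentence or two and a less favourable stated power. No added pupils are required.
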